#### Control condition

For HSOs that do not respond to the initial distributing educational materials strategy and are randomized to the control condition, no additional strategies will occur. If staff in control HSOs or immediate exploration HSOs click on the dissemination email before their landing page access expires (i.e., approximately thirty days after first dissemination email is sent), they will have access to the Phase I training tools (described above) and can proceed to Phase II if they complete the Phase I requirements.

### Outcomes

Guided by the extant literature, our primary dissemination outcome is *adoption*, which Baumann et al. [24] define as occurring when “the individual or organization engages in a number of activities that will lead to the research evidence being integrated into clinical practice and/or policy decisions” (p. 8). Per this definition and our cluster-randomized design, we will examine both *staff-level MIBI adoption* (i.e., number of HSO staff who download the MIBI manual and/or enroll in the online asynchronous MI training) and *organization-level MIBI adoption* (i.e., number of HSOs with staff-level MIBI adoption by 1 + staff). Secondary outcomes are: *staff-level MIBI exploration* (i.e., number of HSO staff who open either dissemination email), *organization-level MIBI exploration* (i.e., number of HSOs with staff-level MIBI exploration by 1 + staff), *staff-level MIBI implementation* (i.e., number of HSO staff who self-report any use of the MIBI with clients at the four-month follow-up survey), and *organization-level MIBI implementation* (i.e., number of HSOs where at least one staff person reports any use of the MIBI with clients at the four-month follow-up survey). Figure 2 illustrates MIBI status progression at the HSO-level. For this study, initial MIBI status will be Pre-Exploration for all HSOs and their staff. Transition to other statuses will be based on information from the project’s enrollment database and four-month follow-up survey using the outcome definitions above.

**Fig. 2 Fig2:**
[figure not shown]
Repeated status assessment for motivational interviewing brief intervention

### Participant timeline, sample size, and recruitment

Figure 1 provides an overview of the participant timeline. Regarding sample sizes, we anticipate approximately 750 HSOs and 3,100 individual HSO staff will eligible and have the opportunity to enroll in the study. Regarding recruitment, HSO points of contact will be sent the initial dissemination email (see Supplemental File 1) via Salesforce in a staggered batch format of up to 180 HSOs in six separate batches. The dissemination email will link to a landing page with information about the study and MI. Participants may choose to click the “Learn More & Enroll” button and be directed to the REDCap (Research Electronic Data Capture) [41] study consent and demographics survey.

#### Blinding (Masking)

HSO staff will not be blinded to study condition. Individuals assigning the scores on the outcomes will be blinded to study condition.

### Data collection and management

#### Staff surveys

Staff-level data collection occurs at two timepoints: baseline and four-month follow-up. After providing online consent, HSO staff will be asked to complete a brief baseline survey via REDCap that includes questions about demographics (age, race, ethnicity, sex assigned at birth, gender, educational attainment, certification/licensure), years of experience working at HSOs, tenure at current HSO, and experience with MI. The three experience questions ask staff to self-report their (a) familiarity (“not at all familiar,” “somewhat familiar,” “moderately familiar,” or “extremely familiar”), (b) experience (“novice,” “moderate,” or “experienced”), and (c) training (checking all that apply from “professional in person conference or training,” “online course or training,” “work mandated training,” “self-taught from literature,” and “another setting” with a text box to describe) related to using MI with clients who have risky substance use behaviors.

Approximately 4 months after the original dissemination email is sent, HSO staff enrolled in the study will receive an invitation to complete a follow-up survey via email. The invitation will direct participants to a REDCap survey that focuses on MIBI implementation and training resource use. The item measuring MIBI implementation asks, “In the last three months, have you completed a MIBI session with a client who displays risky substance use?” with response options of “yes,” “no,” and “unsure.” Responses of “yes” will be coded as MIBI implementation at the staff- and HSO-level. The survey then asks about the use of the four training resources that were made available (MIBI Manual, Tour of MI, SIMmersion, LYSSN). For each resource used, the survey includes five items measuring (a) relevance to the individual’s work, (b) learning how to apply MI to substance use, (c) ease of understanding the content, (d) feelings of preparation to use MI for substance use, and (e) learning foundational principles of MI. These items use a four-point Likert scale ranging from “strongly agree” to “strongly disagree.” For the MIBI Manual, additional questions ask about use of specific worksheets/tools with clients (“yes,” “no,” or “unsure”). For each resource not used, the survey assesses potential barriers: (a) pre-existing confidence in using MI for substance use, (b) competing work demands, and (c) lack of clients with risky substance use. For non-use of the MIBI Manual, additional barriers include manual length and lack of interest. Individuals not using Tour of MI will also be asked about the training being too long and previous completion of a similar training. Additional barriers specific to the two learning platforms will be included, such as not liking virtual simulations as a training method, perceived complexity of the websites, and not wanting feedback on MI skills. All items measuring potential barriers use a four-point Likert scale from “strongly agree” to “strongly disagree.” Participants who complete the follow-up survey will receive a $20 electronic gift card distributed by Virtual Incentives as compensation for their time.

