HSO staff who click the “Learn More and Enroll” button in the dissemination email will be taken to the study’s landing page to provide electronic informed consent, complete a brief baseline demographics survey, and gain access to Phase I resources for approximately thirty days from the time of the initial email invitation. Phase I resources include the MIBI Manual for self-review and no-cost access to the online course, “A Tour of Motivational Interviewing: An Interprofessional Road Map for Behavior Change” (Tour of MI). The MIBI Manual is a comprehensive guide that outlines the MIBI intervention, provides practical tools for conducting the intervention, and requires less than 90 min to review. Tour of MI is a self-paced, four-hour online course developed by the Mid-America Addiction Technology Transfer Center at the University of Missouri-Kansas City School of Nursing and Health Studies. This course offers foundational training in MI, emphasizing collaborative conversations to strengthen a client’s motivation for behavior change and the use of MI techniques within an atmosphere of acceptance and compassion. The course content is applicable across health professionals. Some professions are eligible for 4.0 continuing education credits for a fee (CE; Continuing Medical Education, Continuing Nursing Education, National Association of Social Workers, and NAADAC); a certificate of completion is available if CEs are not provided. If the participant provides documentation confirming prior completion of the Tour of MI, they will be fast-tracked to Phase II.

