### Strengths and limitations

The MOTIVATE CHANGE dissemination experiment has strengths and limitations. Strengths include: (1) its national-level scale, (2) its use of an adaptive non-responder randomization design, (3) its use of actual behavior (i.e., clicks) to assess the primary outcome (i.e., MIBI adoption/preparation) and secondary outcome (i.e., MIBI exploration), and (4) its assessment of outcomes from both organization and individual perspectives. Several limitations should be noted. First, the researchers are the source (i.e., purveyor) of both the distributing educational materials and exploration facilitation strategies, as opposed to AETCs (i.e., intermediaries) being the source; it will not be known whether AETCs are a more effective source for these strategies. Second, the follow-up period will be limited to four-months post-dissemination, so it will be unknown whether implementation will be sustained beyond that period or whether some HSOs can achieve implementation if given a longer time. Third, MIBI adoption/preparation is operationalized as downloading of the MIBI manual and/or initiating the Tour of MI online asynchronous training, both of which may still be considered part of the exploration phase. Fourth, it is possible that a high rate of response during the one-week run-in period may impede our ability to deploy the exploration facilitation strategy. However, we believe the risk of this limitation is low.

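### Implementation is defined as any MIBI use reported at the four-month survey, but the only coded item looks back three months, so use confined to about the first 30 days is counted as none

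*Protocol article*

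**What the plan says.** In the protocol article, the Outcomes section lists implementation among the secondary outcomes. At staff level it is the "number of HSO staff who self-report any use of the MIBI with clients at the four-month follow-up survey". At organization level it is the "number of HSOs where at least one staff person reports any use of the MIBI with clients at the four-month follow-up survey". Neither definition carries a recall limit.

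The Staff surveys section sets the timing: "Approximately 4 months after the original dissemination email is sent, HSO staff enrolled in the study will receive an invitation to complete a follow-up survey". The clock starts at the email, not at enrolment. The item reads "In the last three months, have you completed a MIBI session with a client who displays risky substance use", and the coding rule is "Responses of “yes” will be coded as MIBI implementation at the staff- and HSO-level". No other item enters that rule. The questions on use of specific manual worksheets and tools are collected but not coded as implementation.

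Under Distributing educational materials, staff who consent "gain access to Phase I resources for approximately thirty days from the time of the initial email invitation". The Strengths and limitations section says "the follow-up period will be limited to four-months post-dissemination".

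**The concern.** The definition and the instrument cover different periods. A survey at about month four with a three-month look-back leaves about one month unasked, and that month is when staff enrol and receive the manual and course.

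Use in that month is feasible. Under Distributing educational materials, the manual takes less than 90 minutes to review, the course four hours, and the MIBI itself 15 to 30 minutes to deliver. A staff member who tried it once in week 2 and not again would truthfully answer *no* and be coded as a non-implementer, although the Outcomes definition counts that person. The HSO would also be miscoded if nobody else there reported use, and so would the status progression, which follows the same definitions.

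At stake is what the implementation outcome can claim. The Statistical methods section compares three groups on each outcome, and one of them is defined by early enrolment.

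**Working it through.** The document gives no figure of its own to reproduce here. The check is window arithmetic followed by a sensitivity calculation.

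**Inputs**
- Survey at about 4 months after the first email, taken as day 120 (Staff surveys).
- Look-back of 3 months, taken as 90 days (Staff surveys).
- Enrolment possible from day 0 to about day 30 (Distributing educational materials).
- Immediate exploration HSOs: at least one staff member enrols in the one-week run-in, days 0 to 7 (Distributing educational materials).
- Randomized HSOs: no staff enrolled at the end of the run-in, so enrolment falls in about days 7 to 30 in both arms (Allocation; the Exploration facilitation and Control condition sections keep the same expiry date).

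**Step 1: unmeasured time.** The item covers day 120 − 90 = 30 onward. For a person enrolling on day *e*, unmeasured days = max(0, 30 − *e*), and their share of post-enrolment time is (30 − *e*)/(120 − *e*).

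| Enrolment day | Unmeasured days | Share of post-enrolment time |
|---|---|---|
| 0 | 30 | 30/120 = 25% |
| 7 | 23 | 23/113 = 20% |
| 30 | 0 | 0/90 = 0% |

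Week-1 enrollers therefore lose 23 to 30 days, and enrollers in randomized HSOs lose 0 to 23 days.

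**Step 2: share of users missed.** Step 1 gives shares of time, not of people. Only staff whose sole use fell in the gap are miscoded. Assume, since the document gives no rate, that sessions follow a Poisson process at constant rate *r* per month after enrolment, and let *g* be the unmeasured months, (30 − *e*)/30. Then

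share of true users missed = (1 − e^(−rg)) · e^(−3r) / (1 − e^(−r(g+3))).

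For *r* = 0.1 and *e* = 0 (*g* = 1), the numerator is (1 − e^(−0.1)) · e^(−0.3) = 0.0705, the denominator is 1 − e^(−0.4) = 0.330, and the ratio is 0.214.

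| Sessions per month (assumed) | Day 0 | Day 7 | Day 18.5 | Day 30 |
|---|---|---|---|---|
| 0.1 | 21% | 17% | 10% | 0% |
| 0.5 | 10% | 8% | 5% | 0% |
| 1 | 3% | 3% | 2% | 0% |
| 2 | 0.2% | 0.2% | 0.1% | 0% |

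Day 18.5 is the midpoint of the 7-to-30 range. The loss matters if use is sparse and vanishes if it is frequent. At HSO level it is smaller wherever a colleague reports later use.

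**The case against.** **The Outcomes wording may be only a label.** It sets the threshold (any versus none) and names the survey, and the Staff surveys section then openly gives the item, window and coding. That is a fair reading of intent. But the stated follow-up period is four months and nothing connects it to a three-month window, so a reader of the outcome definition would expect first-month use to count.

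**A fixed look-back has merit.** Days 30 to 120 follow the close of enrolment, so all enrolled staff are asked about the same period. A question about use since access would cover 120 days for a day-0 enroller and 90 for a day-30 enroller. This stands. It is a reason to keep the window and correct the definition.

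**Little use may occur in month one.** Staff are still training then, and the 60-day Phase II access follows course completion, so it falls largely in the covered period. This also stands in part and favours the lower part of the range, but the document does not rule out early use.

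**A reader might infer a bias in favour of facilitation**, on the ground that facilitated HSOs enrol later, after their call, and so lose less time. For example, enrolment on day 8 leaves 22/112 = 20% of time unmeasured and enrolment on day 21 leaves 9/99 = 9%. The document does not support that inference. Both randomized arms share the same enrolment bounds, no enrolment dates are given by arm, and calls may begin directly after randomization. The example sets an early day in one arm against the end of the approximate call window in the other, and it measures elapsed time, not miscoded users.

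**Conclusion.** The mismatch is real. As written, the implementation outcome measures use in the three months before the survey and is labelled as any use. About 30 days are unmeasured, assuming 30-day months and a survey answered on day 120; a later response widens the gap.

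The group defined by week-1 enrolment has the longer gap, so comparisons with immediate exploration are affected unequally. The Statistical methods section already treats those comparisons as open to selection bias, and this adds a measurement difference to it. Staff at those HSOs who enrol after week 1 have the shorter gap. For the randomized contrast, neither direction nor size can be determined.

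The range of about 21% down to 0.2% of true users missed (day-0 enrollers) rests wholly on the assumed constant session rate. The primary adoption outcome and the primary hypothesis are unaffected, so this is a point about the definition and interpretation of a secondary outcome.

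**What to change.** Make the item and the definition agree. Either of two changes does this:

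- **If a survey is still to be sent:** ask about any MIBI session since first access to the materials.
- **If the survey has been fielded as written**, which is likely because Trial status reports that the experiment ended on 5/14/25: restate the staff- and HSO-level outcomes in the Outcomes section as *MIBI use in the three months before the four-month survey*. Limit conclusions to that window, and note that week-1 enrollers have a longer unmeasured period when reporting the three-group comparison.

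The worksheet and tool-use questions could support an additional analysis, but it should be labelled exploratory. Using a worksheet is not the same construct as completing a MIBI session, so that analysis would not recover the missed sessions.

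The cost is one reworded survey item, or one reworded outcome and a sentence of interpretation. Neither adds burden for participants.

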#### Website usage data

The study team will obtain usage data for Tour of MI, SIMmersion, and LYSSN. For Tour of MI, data on completion of each module, full course completion, and quiz scores will be linked to the individual HSO staff member’s study record. Study team members will track the creation of individual accounts for SIMmersion and LYSSN. SIMmersion provides total minutes, level of proficiency, and scores for each simulation session; individual-level averages of proficiency and scores across sessions will be calculated. LYSSN provides transcripts of users’ interactions with each virtual simulation as well as counts of listening statements, motivating questions, affirmations, closed questions, giving information, advising, facilitating, and confrontations. Individual-level averages of MI-consistent and MI-inconsistent statements across sessions will be calculated along with changes in these statements from first to last session.

#### Data management

Data will be extracted from the REDCap system to develop analytic datasets. Logical checks and descriptive analyses will be used to assess errors, inconsistencies, and outliers. As part of the data management process, all constructed variables will be produced (e.g., scale scores, total scores). Distributional properties of outcome variables will be assessed to inform decisions about statistical models. Documentation will be prepared to accompany archived copies of the data. Finally, patterns of missing data will be evaluated. If there is evidence that data are not missing completely at random [42], methods for addressing missing data will be used as described in the section on statistical methods.

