### Statistical methods

Statistical analysis of study outcomes will be conducted using an intention-to-treat approach, meaning all HSOs will be analyzed in the group they were randomized to regardless of whether they receive the exploration facilitation strategy. The primary effect to be estimated for each outcome is its difference between the three study groups (distributing educational materials only, distributing educational materials plus exploration facilitation, and immediate exploration). Prior to estimating effects between these groups, balance on demographic characteristics, HSO characteristics, and other background covariates will be assessed by estimating propensity scores between the immediate exploration group and the combination of the two randomized groups (which may have substantial differences), and between the two randomized groups (which should not have differences if randomization worked as expected). If substantial imbalance is observed, doubly robust effects will be estimated by including both propensity score weights and including aforementioned covariates in the models described next.

Since they were not randomized, the comparability between the distributing educational materials only condition participants and the immediate exploration participants will be evaluated prior to propensity score estimation. Comparison of the distributing educational materials plus exploration facilitation group and distributing educational materials-only control group are causal due to the randomization, while comparison of either of these groups to the immediate exploration group is subject to selection bias. However, this selection bias is in itself interesting, and the analysis results will be used to understand what predicts immediate engagement. Each outcome’s distribution will be assessed to ensure adequate distributional assumptions are made in statistical modeling. If outcomes exhibit strong floor and/or ceiling effects, they can be rescaled to a proportion scale and modeled with zero- and/or one-inflated beta regression [19, 43]. If the missing data analyses uncover issues that should be addressed, we will use either full information maximum likelihood or multiple imputation [42]. In addition, summary statistics will be calculated for individual-level follow-up survey data and usage data for Tour of MI, LYSSN, and SIMmersion.

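### Missing-data methods for the two survey-based implementation outcomes should not wait on evidence against missing completely at random

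*Protocol article*

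**What the plan says.** The Data management section says that missingness patterns will be evaluated, and then: "If there is evidence that data are not missing completely at random [42], methods for addressing missing data will be used". Statistical methods states the condition again, more loosely: "If the missing data analyses uncover issues that should be addressed, we will use either full information maximum likelihood or multiple imputation". Neither section says what happens if the condition is not met.

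The outcomes most exposed are the two implementation outcomes, listed as secondary under Outcomes. The organization-level one is the "number of HSOs where at least one staff person reports any use of the MIBI with clients at the four-month follow-up survey"; the staff-level one counts staff who report such use. The Staff surveys section limits who is asked: "HSO staff enrolled in the study will receive an invitation to complete a follow-up survey via email". On coding it says: "Responses of “yes” will be coded as MIBI implementation at the staff- and HSO-level". It does not say how an unreturned survey is coded. Under Statistical methods, "all HSOs will be analyzed in the group they were randomized to regardless of whether they receive the exploration facilitation strategy".

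**The concern.** Three things are wrong with making the methods conditional in this way.

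- Absence of evidence against MCAR is not evidence for it, least of all when few people contribute to the check.
- A check of missingness uses observed data. The likely problem here is that staff who used the brief intervention are more, or less, willing to return the survey. That dependence runs through the missing answer itself, so an observed-data check cannot detect it unless a recorded variable happens to carry it.
- Both named methods rest on the weaker missing-at-random assumption and remain valid under MCAR. Nothing is gained by waiting for MCAR to be rejected.

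At stake is whether the implementation results carry unaddressed non-response bias because a preliminary look found nothing. Response could plausibly differ by arm: one arm is offered a personal call from a facilitator, and HSO staff are not blinded.

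**Working it through.** **Inputs from the article.** About 750 HSOs (Participant timeline, sample size, and recruitment); adoption of 2–3% from the initial strategy and, more realistically overall, the first 16% (Discussion); 1:1 allocation (Allocation). The article gives no survey response rate and no expected implementation rate, so every such rate below is an assumption.

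**The article's own figures.** 750 × 0.02 = 15 and 750 × 0.03 = 22.5, matching its 15 to 23 HSOs. The 16% figure gives 750 × 0.16 = 120 HSOs.

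**Can a check see outcome-dependent non-response?** A simulation used 120 people, 30% true use, response of 90% in users and 50% in non-users, and an observed binary variable unrelated to use. A 5%-level chi-square check of response against that variable rejected in 4.9% of 4,000 runs. That is its nominal error rate, although the missingness is strongly non-random.

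**Can a check see an arm difference in response?** Assume response of 80% v 65%, and take the article's HSO counts as rough numbers of potential responders. With n per arm and mean proportion p̄ = 0.725,

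power = Φ{[0.15 − 1.96√(2p̄(1−p̄)/n)] / √[(0.80×0.20 + 0.65×0.35)/n]}.

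- n = 60 (120 in total): Φ[(0.15 − 0.160)/0.080] ≈ 45%.
- n = 11 (about 23 in total): Φ[(0.15 − 0.373)/0.188] ≈ 12%.

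Several enrolled staff per HSO would raise these numbers, but such staff are clustered.

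**How far could the handling move an estimate?** Let t be true use among enrolled staff, r1 response in users and r0 response in non-users. Scoring non-response as no use gives t·r1. Complete cases, or imputation without informative predictors, give t·r1 / [t·r1 + (1−t)·r0].

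| t | r1 | r0 | Non-response = no use | Complete cases |
|---|---|---|---|---|
| 30% | 70% | 70% | 21.0% | 30.0% |
| 30% | 80% | 50% | 24.0% | 0.24/0.59 = 40.7% |
| 30% | 90% | 50% | 27.0% | 0.27/0.62 = 43.5% |
| 30% | 50% | 70% | 15.0% | 0.15/0.64 = 23.4% |

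**Between arms.** With equal true use of 30% and response of 80% v 65% unrelated to use, scoring non-response as no use gives 0.30 × 0.80 = 24% v 0.30 × 0.65 = 19.5%, a false difference of 4.5 points. Complete cases give 30% in both arms.

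**On the HSO denominator.** Assume 375 HSOs per arm and 60 adopting (16%), with one enrolled person in each. Then 18% v 30% of adopters becomes 10.8/375 = 2.9% v 18/375 = 4.8% of HSOs.

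**The case against.** The strongest reply is that the article says less than a critic might read into it.

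- A reader might infer that the plan switches between contradictory rules: unreturned surveys count as no use by default and become unknown once the trigger fires. The article states no fallback. Scoring non-response as no use can only be inferred from the outcome definition, the coding of positive answers and the intention-to-treat statement. Complete-case analysis is the other reading. Defining an outcome as a number of reports is ordinary wording and does not conflict with imputing missing reports. This part of the objection stands.
- No formal test is named. The wording in Statistical methods is broad enough for an analyst to act on high or unequal non-response without a significant result. So the power and simulation figures show the limits of one kind of check, not of a specified procedure. The objection stands to that extent. But a broader look at observed data still cannot see dependence on the missing answer.
- A reader might infer that no sensitivity analysis is planned. An analysis plan may exist and the article is condensed, so absence here shows nothing.
- The percentages are assumed and mostly single-group. On the full HSO denominator the gap is only a few points.
- Reach is narrow. Adoption is measured from recorded behavior and exploration from email opens, so the primary hypothesis does not depend on this.

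What remains is the condition itself, which both sections state.

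**Conclusion.** The concern holds in limited form. Making missing-data methods conditional on evidence against MCAR, or on other issues noticed in the data, is a poor rule for the two secondary implementation outcomes. It should be changed, but it does not threaten the primary comparison.

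The size of any bias cannot be stated. The illustrations show only that handling could matter: among enrolled staff, the two simple approaches differ by roughly 8 to 17 points under the assumed rates, and by about 2 points in the HSO-level example. The direction depends on who responds.

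A reader might also conclude that scoring non-responders as no use is the natural primary rule. The documents do not require it, and the 24% v 19.5% example shows that it can create an arm difference where none exists. It belongs among the sensitivity analyses.

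**What to change.** Delete the condition in both Data management and Statistical methods. Fix one method in advance for both implementation outcomes, used whatever the missingness check shows:

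- **Main analysis:** multiple imputation of the survey answer for enrolled non-responders, using arm, batch, baseline survey items and the logged Tour of MI, SIMmersion and LYSSN use described under Website usage data. Derive the HSO-level outcome from the completed staff answers and keep all randomized HSOs in the denominator.
- **Sensitivity analyses, always reported:** non-response scored as no reported use, and best- and worst-case bounds by arm.

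The logged training use makes missing at random more credible but cannot guarantee it, which is why the bounds are needed. They may be wide: with an assumed 100 enrolled, 60 responders and 18 reporting use, they run from 18% to (18 + 40)/100 = 58%.

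The cost is revised wording and a small amount of extra analysis on data already collected. Trial status reports that the experiment has ended, so the rule should be recorded before survey answers are compared by arm, or labeled as a later decision if they already have been.
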